## Abstract

**Background:**

In definitive radiation therapy for head and neck cancer, clinically uninvolved cervical lymph nodes are irradiated with a so-called ‘elective dose’ in order to achieve control of clinically occult metastases. As a consequence of high-resolution diagnostic imaging, occult tumor volume has significantly decreased in the last decades. Since the elective dose is dependent on occult tumor volume, the currently used elective dose may be higher than necessary.

Because bilateral irradiation of the neck contributes to dysphagia, xerostomia and hypothyroidism in a dose dependent way, dose de-escalation to these regions can open a window of opportunity to reduce toxicity and improve quality of life after treatment.

**Methods:**

UPGRADE-RT is a multicenter, phase III, single-blinded, randomized controlled trial.

Patients to be treated with definitive radiation therapy for a newly diagnosed stage T_2-4_ N_0-2_ M_0_ squamous cell carcinoma of the oropharynx, hypopharynx or larynx are eligible. Exclusion criteria are recurrent disease, oncologic surgery to the head and neck area, concomitant chemotherapy or epidermal growth factor receptor inhibitors.

In total, 300 patients will be randomized in a 2:1 ratio to a treatment arm with or without de-escalation of the elective radiation dose and introduction of an intermediate dose-level for selected lymph nodes. Radiation therapy planning FDG-PET/CT-scans will be acquired to guide risk assessment of borderline-sized cervical nodes that can be treated with the intermediate dose level.

Treatment will be given with intensity-modulated radiation therapy or volumetric arc therapy with simultaneous-integrated boost using an accelerated fractionation schedule, 33 fractions in 5 weeks. The primary endpoint is ‘normalcy of diet’ at 1 year after treatment (toxicity). The secondary endpoint is the actuarial rate of recurrence in electively irradiated lymph nodes at 2 years after treatment (safety).

**Discussion:**

The objective of the UPGRADE-RT trial is to investigate whether de-escalation of elective radiation dose and the introduction of an intermediate dose-level for borderline sized lymph nodes in the treatment of head and neck cancer will result in less radiation sequelae and improved quality of life after treatment without compromising the recurrence rate in the electively treated neck.

**Trial registration:**

ClinicalTrials.gov Identifier: NCT02442375.

## Background

In definitive radiation therapy for head and neck cancer, generally two dose-levels are delivered.

A high dose, the so-called “boost dose” to eradicate macroscopic tumor and a lower dose, the so-called “elective dose” to achieve control of clinically occult metastases in cervical lymph nodes. The current equivalent dose in 2 Gy fractions (EQD2) prescribed to the elective volume is 45–50 Gy and is based on literature from the nineteen-fifties [1]. At that time, assessment of the neck only consisted of physical examination due to the lack of sufficiently sensitive diagnostic imaging of lymph nodes.

Today, ultra-sound (US) with fine needle aspirated cytology (FNAC), computed tomography (CT) and magnetic resonance imaging (MRI) provide high resolution anatomical detail and have a high sensitivity and specificity in the detection of cervical lymph node metastases in head and neck cancer [2], even in a neck without palpable lymph nodes [3].

As a consequence of the implementation of high-resolution diagnostic imaging techniques, tumor deposits measuring only a few millimeters are now detected and added to the boost volume. It is therefore plausible that nowadays occult tumor volume in radiologically uninvolved lymph nodes is much smaller than in the era before the implementation of these imaging techniques. However, the radiation therapy dose prescription practice for elective nodal regions has not changed over the years.

Since the dose required to control subclinical disease is dependent on occult tumor volume [4, 5], it would make sense to refine the traditional binary dose prescription to a more gradual one that is proportional to tumor volume. For this purpose, molecular imaging using fluorodeoxyglucose positron emission tomography (FDG-PET) can improve the accuracy of current diagnostic imaging assuming that FDG-uptake represents tumor cell density, or at least is a good surrogate for this [6].

The potential value of FDG-PET imaging in the management of cervical lymph nodes lies in the decision-making process whether borderline-sized nodes should be treated with a boost or elective dose [7]. It is even conceivable that borderline-sized nodes having mild FDG-uptake may not require the maximum dose since they are likely to contain no or only a small tumor volume. An intermediate dose level may be sufficient for such nodes.

Because bilateral irradiation of cervical lymph node regions contributes to dysphagia, xerostomia and thyroid dysfunction in a dose dependent way [8, 9], dose reduction to these regions can open a window of opportunity to reduce toxicity and improve quality of life after treatment [10].

A treatment planning study performed at the Radboudumc showed that de-escalation of the elective dose as proposed in this study protocol, can reduce the dose to normal tissues such as the swallowing musculature, thyroid- and salivary glands (unpublished data). Normal tissue complication probability models from the available literature [11–15] showed that a relevant decrease in toxicity can be expected for xerostomia (absolute up to 14%, relative risk up to 39%), dysphagia (absolute up to 12%, relative risk up to 67%) and hypothyroidism (absolute up to 20%, relative risk up to 50%).

Given these considerations we believe that the traditional binary dose prescription in head and neck cancer is outdated. In this trial, a more gradual dose prescription will be used with de-escalation of the elective radiation dose and the introduction of an intermediate dose-level in the treatment of head and neck cancer. The aim is to investigate whether such a treatment will result in less radiation sequelae and improved quality of life after treatment (expressed as a normalcy of diet) without compromising the recurrence rate in electively irradiated lymph nodes.

## Methods/Design

### Objectives

To determine whether a more gradual dose prescription with de-escalation of the elective radiation dose and the introduction of an intermediate dose-level in the treatment of head and neck cancer will result in less radiation sequelae and improved quality of life after treatment (toxicity) without compromising the recurrence rate in electively irradiated lymph nodes (safety).

### Study design

This is a multicenter, phase III, single-blinded, randomized controlled trial.

Treatment allocation at randomization will be at a ratio of 2:1 in favor of the intervention arm. Randomization will be balanced for institution, tumor-site, T- and N-stage, and human papillomavirus status using minimization with a random element. Randomization and clinical trial data management is provided by the IKNL clinical research department.

A flow chart giving an overview of the study design is shown in Fig. 1.

**Fig. 1 Fig1:**
[figure not shown]
Flow chart giving an overview of the study design. *the reported dose is the equivalent dose in 2 Gy fractions (EQD2)

### In- and exclusion criteria

Adult patients having a new, pathologically proven squamous cell carcinoma located in the larynx, oropharynx or hypopharynx with stage T_2-4_ N_0-2_ M_0_ are eligible for inclusion after written informed consent. Patients must be able to undergo accelerated radiation therapy and have a World Health Organization performance status of 0–2.

Main exclusion criteria are concomitant chemotherapy or epidermal growth factor receptor inhibitors for this tumor, prior anticancer treatment to the head and neck area (surgery, chemotherapy or radiation therapy), previous malignancies or uncontrolled diabetes mellitus.

### Endpoints

Primary endpoint (toxicity): ‘normalcy of diet’ at 1 year after treatment, measured using the performance status scale for patients with head and neck cancer (PSS-HN) [16].

Secondary endpoint (safety): actuarial rate of recurrence in electively irradiated lymph nodes at 2 years after treatment.

Other endpoints:

Acute toxicity (mucositis, dysphagia and skin reaction).

Late toxicity (with focus on xerostomia, dysphagia and hypothyroidism).

Quality of life (general-, xerostomia- and dysphagia related quality of life).

Recurrence (local, regional, loco-regional and distant).

Survival (overall, disease specific and disease free).

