### Risk assessment of lymph nodes

#### Intervention arm

In the intervention arm, lymph nodes will be classified into three risk-levels and will be treated with a corresponding radiation dose. The FDG-PET-scan will guide risk assessment using standardized methods in order to minimize inter-institutional and inter-operator variations.
*High-risk (macroscopic tumor)*: comprises metastatic nodes that will be identified by (1) positive cytology or (2) necrosis on imaging or (3) SUR_max_ ≥ 2.0.

*Intermediate-risk*: comprises lymph nodes of borderline size having intermediate FDG-uptake and will be identified by (1) summed long- and short-axis diameter ≥ 17 mm and (2) SUR_max_ ≥ 1.5 and <2.0 and (3) cannot be high-risk (e.g. positive cytology or necrosis on imaging). These criteria are based on an in-depth risk assessment on recurrence in 1166 electively irradiated nodes in 264 patients. Not overtly pathologic lymph nodes with a summed diameter ≥ 17 mm had an increased risk to recur after elective treatment (Hazard Ratio: 17.8, 95%CI: 5.7–55, *p* < 0.001) [17].

*Low-risk (microscopic tumor)*: comprises elective lymph node regions defined in the protocol based on tumor site and stage and will be delineated according to published guidelines [20].

Retropharyngeal lymph nodes will be evaluated by traditional means as standardized FDG-PET-guided risk-assessment is not applicable to these nodes.

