#### Control arm

In the control arm, no areas of intermediate risk will be identified. Lymph nodes are either assigned to the high-risk (macroscopic) volume or low-risk (elective) volume by traditional means (positive cytology or necrosis on imaging or short-axis diameter ≥ 10 mm, ≥11 mm for subdigastric nodes).

The FDG-PET-scan may be used in the decision making process by means of visual interpretation.

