### Assessment of recurrence

If recurrence is suspected during follow-up, additional imaging by MRI, CT, PET or US with FNAC will be performed whatever is judged necessary by the attending physician. Examination under general anesthesia is performed if deemed necessary. All recurrences must be confirmed by cytology or histology.

Central evaluation will be done for all regional recurrences in order to determine if the recurrence occurred in an electively irradiated lymph node. The exact site of recurrence will be reconstructed by performing co-registration of the planning CT-scan with diagnostic imaging of the recurrence.

All recurrences in electively irradiated lymph nodes will be reported as a serious adverse event since this is the safety endpoint of this trial.

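### The safety endpoint counts recurrences in electively irradiated nodes, but each arm decides by its own rule which nodes are elective, so the two counts are not comparable, in a direction the article does not let one derive

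*Protocol article*

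**What the plan says.** Under Endpoints, the article gives "Secondary endpoint (safety): actuarial rate of recurrence in electively irradiated lymph nodes at 2 years after treatment". The Sample size calculation section plans on 5% at 2 years and treats 10% or more as unacceptable, at a one-sided alpha of 0.10. Safety assurance triggers an interim log-rank comparison after every five such recurrences. Under Assessment of recurrence, "Central evaluation will be done for all regional recurrences in order to determine if the recurrence occurred in an electively irradiated lymph node".

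Which nodes are elective follows from Risk assessment of lymph nodes, and the two arms differ:

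- **Intervention arm:** "In the intervention arm, lymph nodes will be classified into three risk-levels and will be treated with a corresponding radiation dose". A node is high-risk by any of "1) positive cytology or (2) necrosis on imaging or (3) SUR_max_ ≥ 2.0". The intermediate class "comprises lymph nodes of borderline size having intermediate FDG-uptake", operationally "1) summed long- and short-axis diameter ≥ 17 mm and (2) SUR_max_ ≥ 1.5 and <2.0", provided the node is not already high-risk. Size alone does not take a node out of the low-risk volume.
- **Control arm:** "In the control arm, no areas of intermediate risk will be identified". A node is high-risk by positive cytology, necrosis, or a short axis of at least 10 mm (11 mm if subdigastric). There is no SUR threshold, and PET may be read visually.

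Regional recurrence is listed among the other endpoints. It does not drive the stopping rule.

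**The concern.** A randomized comparison of event rates needs an event defined alike in both arms. Here the set of nodes that can produce an event is fixed after allocation, by a rule that depends on allocation. Randomization balances the patients and their nodes, but it cannot balance a definition that changes with the arm.

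The affected nodes matter clinically: the article reports that "Not overtly pathologic lymph nodes with a summed diameter ≥ 17 mm had an increased risk to recur after elective treatment", with a hazard ratio of 17.8 (95% CI 5.7 to 55), and the intermediate class is drawn from that size group. Events are few, so a handful of differently labelled recurrences could move the result. At stake are the stopping rule and the claim that de-escalation does not compromise recurrence in the elective neck.

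**Working it through.** **Step 1: the one fully specified figure on this endpoint.** Safety assurance gives a nominal alpha of 0.042 and a critical value of 1.728. The normal quantile z(1 − 0.042) is 1.728, which agrees. The point does not rest on this figure.

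**Step 2: apply both rules to the same nodes.** The sizes and SURmax values are constructed examples. Each node is cytology-negative, non-necrotic, not retropharyngeal and not subdigastric, and lies in an elective region.

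| Node | Sum of axes | SURmax | Intervention arm | Control arm | Recurrence counts in |
|---|---|---|---|---|---|
| (a) 9 × 7 mm | 16 mm | 2.2 | High-risk | Elective, unless visual PET upgrades it | Control only |
| (b) 9 × 9 mm | 18 mm | 1.7 | Intermediate | Elective, unless visual PET upgrades it | Control; intervention only if intermediate nodes count |
| (c) 12 × 11 mm | 23 mm | 1.2 | Low-risk | High-risk (short axis 11 mm) | Intervention only |
| (d) 12 × 11 mm | 23 mm | 1.7 | Intermediate | High-risk | Neither; intervention only if intermediate nodes count |

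Node (a) lowers the intervention count relative to control and node (c) raises it. Nodes (b) and (d) depend on a rule that the article does not state. Counting intermediate nodes aligns (b) but makes (d) differ, and leaves (a) and (c) as they are. Clarifying the intermediate class is therefore necessary but does not by itself make the arms comparable.

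**Step 3: how many events are involved.** With 300 patients at 2:1, there are 100 control and 200 intervention patients. At 5%, control yields 100 × 0.05 = 5 events. Intervention yields 200 × 0.05 = 10 events at 5% and 200 × 0.10 = 20 at 10%.

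**Step 4: illustration of size.** Let f be the net share of intervention-arm events that go uncounted. The article gives no value for f, so it is an assumption. The counted intervention rate is p2 = 0.10 × (1 − f), against p1 = 0.05.

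Power = Φ[(p2 − p1 − 1.2816 × SE0) / SE1], where SE0 = √[p̄(1 − p̄)(1/100 + 1/200)], p̄ = (100p1 + 200p2)/300, and SE1 = √[p1(1 − p1)/100 + p2(1 − p2)/200].

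- f = 0: p̄ = 0.0833, SE0 = 0.03385, SE1 = 0.03041. Power = Φ[(0.05 − 0.04338)/0.03041] = Φ(0.218) = 59%.
- f = 0.2: p2 = 0.08, p̄ = 0.07, SE0 = 0.03125, SE1 = 0.02903. Power = Φ[(0.03 − 0.04005)/0.02903] = Φ(−0.346) = 36%.

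| Net share f (assumed) | Counted rate | Power, two proportions | Power, log-rank (Schoenfeld) |
|---|---|---|---|
| 0 | 10% | 59% | 66% |
| 0.1 | 9% | 48% | 54% |
| 0.2 | 8% | 36% | 41% |
| 0.3 | 7% | 26% | 28% |

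These figures take a single analysis with all patients followed to 2 years and ignore the interim looks. At f = 0.2 the loss is 0.2 × 20 = 4 events.

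The shift can equally go the other way. If reclassification added a net 20% to the intervention count, a true 5% would appear as 5% × 1.2 = 6%, and a safe treatment would look worse than it is.

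**The case against.** The strongest defence is that the endpoint fits the stated question. The objectives ask about recurrence in electively irradiated nodes, that is, whether the lower elective dose controls the nodes that receive it, and PET-guided reclassification is part of the strategy under test. This stands as a reason to keep the endpoint. It does not make the two arms' counts comparable.

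Second, an arm-neutral measure already exists: regional recurrence is an endpoint, and all regional recurrences are centrally evaluated. A rise masked by labelling could still be seen there. That also stands, and it makes the fix cheap. But regional recurrence feeds neither the interim rule nor the 5% versus 10% criterion.

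Third, discordance may be modest. Visual PET reading in control and pre-treatment ultrasound with cytology would move some nodes, and retropharyngeal nodes are judged by traditional means in the intervention arm too. This limits the size without removing the problem; node (c) is untouched by any SUR-based upgrade.

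A reader might infer three stronger things that the article does not support:

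- **That the bias favours the intervention.** The rules move nodes in both directions. Any formula with removals from the intervention count alone models half of the mismatch.
- **That recurrences in intermediate-risk nodes are excluded.** The article does not say so; it is silent.
- **That the hazard ratio of 17.8 measures what is lost.** It applies to not overtly pathologic nodes with a summed diameter of at least 17 mm, without a SUR condition. Such nodes with SURmax below 1.5 stay countable in the intervention arm, and some have a short axis that takes them out of the elective volume in control.

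**Conclusion.** The point holds as a problem of comparability. The endpoint, the central-review question and the stopping rule all rest on a label that the two arms assign by different criteria. Following the plan as written gives a safety contrast that mixes the effect of the lower dose with the effect of relabelling. This is more than detail left to a fuller document, because both sets of rules are stated and they conflict as an event definition.

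Direction and size are unknown. The fall from about 59% to 36% power (66% to 41% by log-rank) is an illustration that rests on an assumed net 20% of intervention-arm events going uncounted; it is not an estimate. A reader might go further and conclude that a real doubling would be hidden, or that the endpoint should be replaced. The first needs half of the intervention-arm events to be lost net, for which the article gives no basis. The second would bring failures in boosted nodes into the endpoint that tests elective dose, and would detach it from its 5% and 10% planning rates.

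**What to change.** 1. Keep the current endpoint as the test of the elective volume, and state that recurrences in intermediate-risk nodes count as safety events.
2. Add a prespecified arm-neutral safety comparison that the final safety conclusion and the safety committee's interim review must also consider. Use either total regional recurrence, or recurrence in any node that was cytology-negative and non-necrotic at baseline (the criteria both arms share), whatever volume it was assigned to.
3. If the second option is chosen, have central review classify the recurrent node on the baseline planning PET/CT, by reviewers unaware of the arm.
4. State a separate reference rate for the added comparison.

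The cost is a change to the endpoint wording, the central-review form and the safety committee's instructions. The planning PET/CT and the central evaluation of regional recurrences are already in the plan, and the node rules and dose levels are not touched. The downside is that the arm-neutral count includes some failures in boosted nodes, so the 5% and 10% planning rates apply only to the current endpoint. Counting intermediate-risk nodes may also require a check that 5% remains a fair planning rate there.

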### Sample size calculation

This study was designed to detect a 10-point difference on the PSS-HN ‘normalcy of diet’ score at 12 months after radiation therapy with a power of 90% at a two-sided significance level of 0.05. An average ‘normalcy of diet’ score of 70 is expected after standard treatment. To achieve this significance level with an unequal randomization ratio (2:1), a total of 300 patients needs to be included.

The current rate of recurrence in electively irradiated lymph nodes was estimated to be 5% at 2 years after treatment [17]. An equal rate of recurrence is expected in the intervention arm, despite elective dose de-escalation. A recurrence rate of ≥10% will be considered clinically relevant and unacceptable. This difference can be detected with the number of patients planned for the primary outcome of the study and a one-sided α = 0.10.

The total duration of this trial is estimated to be 6 years (4 years accrual, 2 years follow-up).

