### Statistical analysis

All analyses concerning treatment effects will be done according to the intention to treat principle. The student’s t-test will be used to compare ‘normalcy of diet’ scores at 1 year after treatment, the primary endpoint of this trial. A Kaplan-Meier estimate will be calculated for the actuarial rate of recurrence in electively irradiated lymph nodes at 2 years after treatment. Actuarial rates on recurrence and survival will be determined by the date of histopathological diagnosis. Differences between the treatment arms will be assessed using the log-rank test.

For each quality of life questionnaire, data will be included in the analysis if a patient filled in the questionnaire at least at start and at one time-point during the study. Differences in quality of life over time between the intervention- and control arm will be analyzed by using a linear mixed model for repeated measurements. Difference in quality of life scores ≥10 points will be considered clinically relevant [32].

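### The primary t-test on the 1-year diet score leaves out the earlier PSS-HN scores and, unless values are imputed, every patient without a 12-month score, despite the intention-to-treat claim

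*Protocol article*

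**What the plan says.** The Sample size calculation section of the protocol article states: "This study was designed to detect a 10-point difference on the PSS-HN" normalcy-of-diet score at 12 months, "with a power of 90% at a two-sided significance level of 0.05". It expects a mean of 70 in the standard arm and concludes that "a total of 300 patients needs to be included". Allocation is 2:1 (Study design), so 200 and 100 patients. The section gives no SD and no allowance for patients without a 12-month score.

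The Statistical analysis section states: "All analyses concerning treatment effects will be done according to the intention to treat principle". It then names a Student's t-test for the "scores at 1 year after treatment, the primary endpoint of this trial". It mentions no covariate, no use of earlier scores and no handling of a missing 1-year score.

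Table 2 (Follow-up) schedules the PSS-HN before treatment and at 3, 6, 12 and 24 months. For quality of life over time, the Statistical analysis section names a linear mixed model. It limits the data to patients with a questionnaire at the start and at least one later one.

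**The concern.** The primary endpoint is one score, taken a year after treatment for T2-4 N0-2 disease. Recurrence and survival are themselves endpoints of the trial, so some patients will foreseeably die, relapse or miss the visit before the score is due.

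A two-sample t-test needs an observed value for each patient. Without imputation it compares only those who have a 12-month score, which does not sit well with an unqualified intention-to-treat statement. Recurrence in the de-escalated neck is the trial's safety question and toxicity is its efficacy question. Both could affect who has a score and what it would have been. If so, the comparison of observed scores could be biased; the article does not allow a direction or size to be given.

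The second cost is precision. A pre-treatment score and two post-treatment scores are collected before month 12, and the named primary test uses none of them.

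**Working it through.** **Inputs stated in the article.** Difference 10 points; two-sided alpha 0.05; power 90%; allocation 2:1; total 300.

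**Inputs not stated, and assumed here.** The SD; the share of patients without a 12-month score, taken as equal in both arms; and the correlation r between the pre-treatment and 12-month scores.

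**Step 1: the article's own figure.** With 2:1 allocation the variance of the difference is SD² × (1/(N/3) + 1/(2N/3)) = 4.5 × SD²/N. The total to be analysed is therefore

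N = 4.5 × ((1.960 + 1.282) × SD/10)².

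Controls are rounded up to a whole number and doubled for the other arm:

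| SD | N by formula | N rounded | Loss that 300 would absorb |
|---|---|---|---|
| 25 | 295.5 | 297 | 1% |
| 24 | 272.4 | 273 | 9% |
| 22.5 | 239.4 | 240 | 20% (240/0.8 = 300) |

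With exactly zero loss, 300 corresponds to an SD of 25.2. With 10% loss it corresponds to 23.9. The total of 300 is thus compatible with several pairs of SD and loss, and the article does not say which pair was used.

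**Step 2: what the named test uses.** Setting the Statistical analysis section beside Table 2:

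- Pre-treatment, 3-month and 6-month PSS-HN: collected, not used by the t-test.
- 12-month PSS-HN: used where observed.
- Patients without a 12-month score: contribute nothing unless a value is imputed, and no imputation rule is shown.

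**Step 3: illustration of the cost.** Take SD 25 and 15% without a 12-month score, leaving 85 controls and 170 intervention patients (255 in total).

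Standard error without adjustment: 25 × √(1/85 + 1/170) = 25 × 0.1328 = 3.32. The ratio 10/3.32 is 3.01, and power is about 85%.

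Adjusting for the pre-treatment score reduces the residual SD to SD × √(1 − r²):

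| r | Residual SD | Standard error | 10/SE | Power |
|---|---|---|---|---|
| 0 (t-test) | 25.0 | 3.32 | 3.01 | 85% |
| 0.3 | 23.8 | 3.17 | 3.16 | 88% |
| 0.5 | 21.7 | 2.88 | 3.48 | 93% |

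Power is from the noncentral t distribution; the normal approximation agrees to within half a percentage point.

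These figures cover baseline adjustment alone, in the same 255 patients. Any information that the 3- and 6-month scores carry about patients without a 12-month score is not counted.

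**The case against.** **The 90% power.** A reader might infer that 300 is the number that must be analysed, so that any loss takes the trial below its stated power. The article does not support this. An SD of about 25 follows only if zero loss is assumed first, so the lack of reserve is then an input and not a result. An SD of about 24 with 9-10% loss, or 22.5 with 20% loss, fits 300 equally well. An unstated SD or attrition allowance is also detail that a condensed article may leave to the full protocol. This objection stands, and no power failure is claimed here.

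**Imputation may be specified elsewhere.** A t-test can be run on imputed values, and the full protocol or analysis plan may say so. This stands too, which is why the point is conditional on imputation. It does not answer the loss of precision: the test named in the article is unadjusted whatever happens to missing values.

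**A single-visit comparison matches the endpoint.** It does, and it is a valid test when scores are complete. The proposal keeps the same endpoint and contrast and changes only the estimator.

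**The earlier scores may already be analysed.** Table 2 lists the PSS-HN under dysphagia-related quality of life, so the mixed model for quality of life may cover it. The Functional assessments section classes it as functional performance, so coverage is arguable. Even if it is covered, that analysis is separate from the primary test.

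**A mixed model does not deal with death.** Correct. It assumes data missing at random and implicitly models scores that patients who died could not have had. Giving deaths the worst score answers a different question and is a choice for the trial team. The model proposed here does not settle it.

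**Conclusion.** The point holds for the primary analysis method. As named, the test is unadjusted, makes no use of the pre-treatment, 3-month and 6-month scores and, without imputation, is restricted to patients with a 12-month score. That restriction is in tension with the intention-to-treat statement.

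The cost is moderate. Under the assumed SD of 25 and 15% missing, baseline adjustment alone is worth about 3 percentage points of power at a correlation of 0.3 and about 8 at 0.5 (85% to 88% or 93%). The article gives no SD, attrition rate or correlation, so these figures illustrate the gain and do not estimate it. The possible bias from selective missingness cannot be sized from the article.

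**What to change.** Keep normalcy of diet at 1 year as the primary endpoint. Replace the t-test with the 12-month between-arm contrast from a linear mixed model on the 3-, 6- and 12-month PSS-HN scores, with arm, visit, arm-by-visit interaction and the pre-treatment score. Include every randomized patient with at least one post-treatment score, in the arm to which they were assigned, and not only those with complete data. State that the analysis relies on data being missing at random, and state separately how deaths before 12 months are handled. If the full protocol already has an imputation rule for the 1-year score, reconcile it with this model.

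The cost is a few sentences in the analysis section. The article already names this type of model for quality of life, Table 2 already schedules every score, and no extra patients or visits are needed.

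### Recurrence of 10% or more is called unacceptable, but the only planned safety tests are log-rank tests of equal arms, which can signal harm but cannot show that 10%, or a 5-point excess over control, has been ruled out

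*Protocol article*

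**What the plan says.** All references are to the protocol article.

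- *Endpoints* makes safety a rate: "Secondary endpoint (safety): actuarial rate of recurrence in electively irradiated lymph nodes at 2 years after treatment".
- *Sample size calculation* gives the planning values: "The current rate of recurrence in electively irradiated lymph nodes was estimated to be 5% at 2 years after treatment" and "An equal rate of recurrence is expected in the intervention arm, despite elective dose de-escalation". It then sets the limit, "A recurrence rate of ≥10% will be considered clinically relevant and unacceptable", and adds: "This difference can be detected with the number of patients planned for the primary outcome of the study and a one-sided α = 0.10". No power is given for this comparison.
- *Methods* (abstract) fixes the size: "In total, 300 patients will be randomized in a 2:1 ratio", that is 200 intervention and 100 control patients.
- *Statistical analysis* plans an estimate, "A Kaplan-Meier estimate will be calculated for the actuarial rate of recurrence in electively irradiated lymph nodes at 2 years after treatment", and a test, "Differences between the treatment arms will be assessed using the log-rank test".
- *Safety assurance* adds a log-rank look after every 5 elective-node recurrences. Each look uses a nominal 0.042 (critical value 1.728), for an overall one-sided 0.10. A safety committee advises on continuation.
- *Objectives* asks for less toxicity without a worse recurrence rate in the electively irradiated nodes.

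**The concern.** The objective needs a positive safety statement: recurrence has not been compromised. The article gives a yardstick for that statement, 10% against an expected 5%. Its tests, however, have equal hazards as the null hypothesis. Rejection is evidence of harm. Failure to reject is evidence of very little unless power at the unacceptable scenario is high, and the article gives no power.

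No stated analysis sets a confidence limit against 10%, or against the 5-point gap between 10% and 5%. At stake is a claim that de-escalation is safe which rests on a non-significant test with only moderate power at the rate the protocol itself calls unacceptable.

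**Working it through.** **Inputs.** From the article: control 5%; unacceptable rate 10%; 200 vs 100 patients; one-sided α = 0.10 (z = 1.2816); interim critical value 1.728 after every 5 events; 4 years' accrual. Assumed, because the article does not state them: constant hazards, 24 months' follow-up for each patient and no losses. A range for losses is given in step 4.

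**1. The plan's own figures.** 1 − Φ(1.728) = 0.0420, so the nominal level reproduces. With equally spaced looks at 1.728, the overall one-sided error is 0.100 at 4 looks (20 events) and 0.113 at 5 looks (25 events). The detectability statement has no power, so there is nothing to reproduce for it.

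**2. Chance that the log-rank test flags 10% vs 5%, single look.**
- Hazard ratio = ln 0.90 / ln 0.95 = 2.05.
- Expected events = 100 × 0.05 + 200 × 0.10 = 25.
- Schoenfeld: √(25 × 1/3 × 2/3) × ln 2.05 − 1.2816 = 2.357 × 0.720 − 1.2816 = 0.415, and Φ(0.415) = 66%.
- Two-proportion formula: 59%.
- Simulated log-rank test: 60%.

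The Schoenfeld value is optimistic with so few events, so 60% is used below. By the two-proportion formula, 80% power would need about 573 patients.

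**3. The same with the sequential boundary.** The simulation used uniform accrual over 48 months and a look at 1.728 after every 5th event. Runs of 3,000 to 10,000 trials flagged 10% vs 5% in 45% to 48% of trials on the interim looks alone. Adding a final look at 1.728, which is an assumption, gave 49% to 51%.

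So between about 40% (single look) and 55% (interim looks only) of trials at the unacceptable scenario would end without a harm signal.

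**4. What the data could show: (a) intervention arm against 10%.** Exact binomial, one-sided 90% upper limit below 10%:

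| Evaluable | Passes with at most | Upper limit | Pass if truth is 10% | Pass if truth is 5% |
|---|---|---|---|---|
| 200 | 14 | 9.9% | 9.3% | 92% |
| 190 | 13 | 9.8% | 8.7% | 90% |
| 180 | 12 | 9.7% | 8.0% | 88% |
| 160 | 10 | 9.5% | 6.7% | 82% |

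**5. What the data could show: (b) between-arm difference against 5 points.** With 5% in both arms:
- SE = √(0.05 × 0.95 × (1/100 + 1/200)) = 0.0267.
- Power = Φ(0.05/0.0267 − 1.2816) = Φ(0.592) = 72%.
- 80% power would need 387 patients and 90% would need 564.

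If both (a) and (b) are required, power cannot exceed that of (b), about 72%.

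**The case against.** The strongest reply is that 10% was never meant as a free-standing limit. The sentence after it speaks of a difference, so 10% is the alternative to a 5% control rate, and no log-rank test contains its own alternative. The objective is comparative, and a randomised comparison is the right primary evidence. The Kaplan-Meier rate is on the same scale as the limit, and a confidence interval for it may well stand in the full protocol or analysis plan. Central review of regional recurrences, serious-adverse-event reporting and an independent committee add protection.

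Much of this stands, and it rules out some stronger readings that a reader might infer:

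- *That the log-rank test fails because it flags only about 10% of trials when both arms are at 10%.* There is then no between-arm harm, and a flag rate near α is correct behaviour.
- *That an intervention arm at 6% or 7% is acceptable whatever the control rate, and is usually flagged wrongly when control is 2%.* No section calls every rate below 10% acceptable. Recurrence three times that of control is something a comparative test should detect. With the documented boundary, 6% vs 2% is flagged in only about 32% of trials on interim looks and under 50% with a final look.
- *That the article commits to declaring safety on a non-significant test.* It does not say so. It states no rule for the safety conclusion and leaves the log-rank test as the only inferential result.

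The reply does not remove the point. Read comparatively, the unacceptable result is an excess of about 5 points, and a test of equality does not exclude that either. Nor is this merely detail left to an analysis plan: the article itself fixes the yardstick, the tests and the claim that the difference can be detected, and these do not fit together.

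**Conclusion.** The concern holds in this form. The stated tests monitor for harm. They cannot establish that the intervention arm is below 10%, nor that it is within 5 points of control. At 10% vs 5% they flag harm in about 60% of trials with a single one-sided 0.10 look and about 45% to 51% with the 1.728 boundary, so a non-significant result is not evidence that recurrence is uncompromised.

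The planned sample can support a direct statement against 10% (about 92% power at a true 5%; 82% to 90% with 160 to 190 evaluable patients). It supports the randomised statement less well (about 72%). These figures assume constant hazards and 24 months' follow-up. Apart from the stated range for (a), they assume no losses, and the 72% is a normal approximation.

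**What to change.** In *Sample size calculation* and *Statistical analysis*, state that the safety conclusion rests on confidence bounds and not on a non-significant log-rank test. Suggested wording:

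*The safety conclusion will be based on (a) the one-sided 90% upper confidence bound of the intervention-arm 2-year rate of recurrence in electively irradiated nodes, compared with 10%, and (b) the between-arm difference in 2-year rates with its one-sided 90% upper bound, compared with 5 percentage points. Safety will not be concluded from (a) alone. A non-significant log-rank test will not be taken as evidence of safety.*

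Replace the detectability sentence with the design's properties: about 92% power for (a) if the true rate is 5% with 200 evaluable patients (82% to 90% with 160 to 190), about 72% for (b) if both arms are at 5%, and about 60% for a single one-sided 0.10 log-rank test to flag 10% vs 5%. Leave the log-rank test and the interim boundary as they are, described as the harm monitor.

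Cost: protocol and analysis-plan wording and two bounds from data already collected, with no extra patients. The downside is that the stated safety assurance becomes less favourable. Bound (a) is not a randomised comparison, which is why (b) must stand beside it. Raising (b) to 80% power would take 387 patients, and that is a separate decision.
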